#### Dissemination phase

To inform on the design and scale-up of community-based mother-newborn care in Uganda.

**Hypothesis: H1:** Implementation of an integrated care package of five home visits by a CHW during pregnancy and the neonatal period to deliver one-on-one health messages and promote linkage to the health facility improves the following maternal-newborn care practices by at least 20% in two years amongst the target population in rural Uganda:

• % of pregnant women attending ANC at least four times (from 40% to 60%);

• % of pregnant women who get a skilled attendance at delivery (from 30% to 50%);

• % of mothers who put nothing on the cord (to get baseline figures during formative research);

•% of newborns who are managed in skin-to-skin contact after delivery (to get baseline figures during formative research);

• % of mothers and babies who receive postnatal care (from 12% to 50%).

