### Sample and sample size

To evaluate the effect of the intervention, practice differences and changes will be determined as differences in proportions between intervention and control areas. With 80% power and 95% significance level to detect, for example, an increase in attendance four times at ANC from 40% to 60% assuming a coefficient of variation (k) of 0.25 between clusters (parishes), this will require some 60 interviews per cluster in each intervention arm for each practice survey. Similarly, to detect an increase in skilled attendance at birth from 30% to 50%, again with a k of 0.25, some 25 interviews have to be performed. To detect in increase in postnatal care from 12% to 24%, with a k of 0.25, some 30 mothers have to be interviewed. Note that the study is not powered for mortality evaluation. The number of clusters was fixed *a priori* because those were the available ones, and the sample size estimations mainly focused on the cluster size for each outcome for an 80% power.

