### Primary outcomes

1. In ANC

– % of pregnant women attending ANC two, four or more times

– % of pregnant women who know at least two danger signs of pregnancy

– % of pregnant women who prepare for birth

2. In the intrapartum period

– % of pregnant women who have a skilled attendant at delivery

– % of women who went to the HC in an emergency

3. In the postnatal period

– % of babies who are initiated on breast-feeding in the first six hours of birth

– % of babies who are exclusively breastfed during the neonatal period

– % of babies whose first bath was delayed for six and twenty-four hours

– % of mothers who put nothing on the cord

– % of mothers who know at least three neonatal danger signs

– % women whose children were managed in skin-to-skin contact after delivery.

– effectiveness of sepsis management (special studies to determine: maternal and CHW knowledge, compliance and timing of referral, and adequacy of treatment following referral)

Table 4 outlines in details all intermediate outcomes that will be evaluated in the study.

**Table 4 T4:** Study outcomes

**Area in the continuum of care**	**Outcome to be evaluated**

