	**NB. Analysis to be done separately for home and health facility births**
Antenatal care	• % of pregnant women attending ANC two, four or more times
	• % of pregnant women who know at least two danger signs of pregnancy
	• % of pregnant women who prepare for birth*
	• IPT in pregnancy
	• ITN use in pregnancy
	• Tetanus toxoid coverage
	• Uptake of VCT % of mothers who tested for HIV during pregnancy
	• Uptake of IPT - by number of doses
Intrapartum care	• % of pregnant women who have a supervised delivery
	• % of pregnant women who deliver at a health unit
	• % of babies whose cord was cut with a clean instrument
	• % of babies who are immediately dried at birth
	• % of babies who are immediately wrapped after birth
	• % of babies who are born on a clean surface
	• % of home births attended by two assistants
	• % of women who went to the HC in an emergency
Postnatal care	• % of babies whose cord was cut with a clean instrument
	• % of babies who are initiated on breastfeeding within one and twenty-four hours of birth
	• % of babies who are exclusively breastfed during the neonatal period
	• % of babies whose first bath was delayed for six and twenty-four hours
	• % of mothers who put nothing on the cord
	• % of mothers who know at least three neonatal danger signs
	• % of babies who are immediately dried at birth
	• % of babies who are immediately wrapped after birth
	• % of babies who are born on a clean surface
	• % of home births attended by two assistants
	• % women whose children were managed in skin-to-skin contact after delivery
	• mothers who received counselling regarding family planning by six weeks postnatally
	• % of babies who were taken for care if they were ill
	• % of babies referred to health facility by CHW that reach, and timeliness of reaching
Impact level	newborn deaths and stillbirths (note not powered to measure significant reduction in NMR) but we will explore each maternal and newborn death using the VASA and case–control study for, for example, intervention efficacy.
	Neonatal mortality rates will be calculated by intervention and comparison areas

*Birth preparedness will be operationalized through having made plans for where to deliver, transport, and preparing baby/delivery materials. IPT, intermittent presumptive treatment; ITNs, insecticide-treated nets; NMR, neonatal mortality rate; VASA, verbal and social autopsies; VCT, voluntary counselling and testing.

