### Hypothesis testing

The primary analysis for each outcome will be intention-to-treat, which will be defined by a woman’s village of residence. All analyses will account for the cluster-randomized design using random effects logistic regression and will be carried out both with and without adjustment for potential confounders. The estimated effect of the intervention will be presented as a relative risk together with a 95% confidence interval (CI). Logistic regression will be used to explore whether the hypotheses stated below are true or not, and each will be adjusted for intraclass correlation (ICC), coefficient of variation (k), socio-economic status and other potential confounders. The hypotheses are that: the intervention increases

1. % of pregnant women attending ANC at least four times (from 40% to 60%)

2. % of pregnant women who get a skilled attendance at delivery (from 30% to 50%);

3. % of mothers and babies who receive postnatal care (from 12% to 50%).

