### Additional analyses

GIS and socio-economic data are already being collected in the DSS and thus provide a good opportunity to undertake these analyses. In the control area, data analysis will also be done by doing a before-and-after comparison to estimate the effect of only health facility improvement on maternal and neonatal care facilities. Subgroup analyses estimating separate intervention effects for facility- and home-based deliveries.

Analysis will also be done taking account of the quality of the intervention received, as assessed by the process indicators and number of visits received. Because some study participants are highly mobile and some women will move from their place of residence to their parents’ or in-laws’ houses for delivery of the baby, it is envisaged that there may be significant movements across the arms of the trial (that is, some women will move from intervention to control areas and vice versa) during the intervention period. This movement can be tracked using our surveillance system. Thus we will also compare outcomes subdividing women and newborns into the following groups: whether the visits were only pre-delivery or only post-delivery or both, and whether the woman received all five visits, only four, three or two or less visits. However, the main analysis will be based on intention to treat so women who are enrolled in an intervention area, but move to a control area for delivery, will be included in the intervention group.

In addition, analysis will also be done of the mean practice score (a numerical outcome) will be carried out using random effects (multilevel) models that explicitly model the similarity between individuals in the same cluster; (these are not suitable for binary outcomes).

For all statistical determinations, significance levels will be established at 5% level of significance. Coefficient of variation will be reported.

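### The protocol gives three conflicting sets of confirmatory outcomes (five, three and twelve), with differing definitions, and tests each at 5% without saying what counts as success

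*Protocol article*

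**What the plan says.** All references are to the protocol article.

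- **Hypothesis H1** (under Dissemination phase) states that the package "improves the following maternal-newborn care practices by at least 20% in two years" and names five: four or more antenatal (ANC) visits, skilled attendance, nothing on the cord, skin-to-skin contact, and postnatal care (12% to 50%).
- **Sample and sample size** covers three: ANC 40% to 60%, skilled attendance 30% to 50%, and postnatal care 12% to 24%.
- **Hypothesis testing** states "The primary analysis for each outcome will be intention-to-treat" and lists the same three, with postnatal care again at 12% to 50%. Cord care and skin-to-skin contact are not listed.
- **Primary outcomes** has twelve bullets: three antenatal, two intrapartum, seven postnatal. Two carry double cut-offs: the ANC percentage is "of pregnant women attending ANC two, four or more times", and first bath is delayed by 6 and by 24 hours. One, sepsis management, is a bundle of special studies. Receipt of postnatal care is absent.
- **Study outcomes** also places process indicators in the primary evaluation.
- **Breastfeeding initiation** is the percentage "of babies who are initiated on breast-feeding in the first six hours of birth" in Primary outcomes, but "of babies who are initiated on breastfeeding within one and twenty-four hours of birth" in Table 4. Skilled attendance in the primary list becomes supervised delivery in Table 4.
- **Additional analyses** sets one level for every test: "For all statistical determinations, significance levels will be established at 5% level of significance".

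**The concern.** A reader cannot tell from the text which results would confirm the hypothesis. The three lists differ in length and content, and neither of the shorter ones is contained in the longest, because postnatal care appears in both shorter lists and not in the primary list. No section ranks the outcomes or says whether one, several or all must succeed. With 5% applied to each test, a favourable result on any one of many items, or on whichever cut-off or definition suits, could later be presented as the primary finding. The trial is meant to inform national scale-up, so an ambiguous claim of success would carry weight.

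The conflicting target for postnatal care adds to this. A rise from 12% to 24% is what the trial was sized for, yet it falls far short of the 50% in the hypothesis, and the text does not say which of the two a result would be judged against.

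**Working it through.** **1. The lists side by side**

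| Outcome | H1 | Sample size | Hypothesis testing | Primary outcomes |
|---|---|---|---|---|
| ANC, four or more visits | yes | yes | yes | yes, with a second cut-off |
| Skilled attendance | yes | yes | yes | yes |
| Postnatal care | to 50% | to 24% | to 50% | absent |
| Nothing on the cord | yes | no | no | yes |
| Skin-to-skin contact | yes | no | no | yes |
| Other items | none | none | none | eight |

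**2. Reproducing the stated sample sizes**

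Inputs from Sample and sample size: 80% power, 5% significance (taken as two-sided), and the statement "assuming a coefficient of variation (k) of 0.25 between clusters (parishes), this will require some 60 interviews per cluster". The site has 18 parishes; c = 9 per arm is inferred from an even split. The unmatched cluster formula, solved for m interviews per cluster, is

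m = [p0(1−p0) + p1(1−p1)] / [(c−1)(p1−p0)²/K − k²(p0² + p1²)], with K = (1.960 + 0.842)² = 7.849.

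- ANC: 0.48 / (0.04077 − 0.03250) = 58.0, so 59 (stated 60)
- Skilled attendance: 0.46 / (0.04077 − 0.02125) = 23.6, so 24 (stated 25)
- Postnatal care to 24%: 0.288 / (0.01468 − 0.00450) = 28.3, so 29 (stated 30)

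All three reproduce to within one interview, each sized at an unadjusted 5%.

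**3. Chance of at least one false positive if the package has no effect**

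For n independent tests this is 1 − 0.95ⁿ in either direction and 1 − 0.975ⁿ for a false benefit.

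| n | Either direction | False benefit |
|---|---|---|
| 3 | 14.3% | 7.3% |
| 5 | 22.6% | 11.9% |
| 12 | 46.0% | 26.2% |

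These practices are probably positively correlated. Simulating twelve equally correlated normal test statistics (400,000 draws) gives:

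| Correlation | Either direction | False benefit |
|---|---|---|
| 0.3 | 39.8% | 20.3% |
| 0.5 | 31.8% | 16.0% |
| 0.7 | 23.2% | 11.6% |

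The rates for a single test are 5% and 2.5%.

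**4. Power if three primary outcomes share 5%**

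The strictest Holm step is 5%/3 = 0.0167, critical value 2.394.

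*Parish basis of step 2.* Power = Φ(√[(c−1)(p1−p0)²/V] − critical value), with V = [p0(1−p0) + p1(1−p1)]/m + k²(p0² + p1²) and m = 60, 25 and 30. The square-root term is 2.811, 2.841 and 2.858. Power is 80%, 81% and 82% at 5%, and 66%, 67% and 68% at 5%/3.

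*Village basis.* The article gives neither interviews per village nor a village-level k, so both are assumptions. Take 17 women per village (60 × 9 / 31 = 17.4) and 32 control and 31 intervention villages. The variance of the difference is [p0(1−p0)/17 + k²p0²]/32 + [p1(1−p1)/17 + k²p1²]/31. For ANC, 40% to 60%:

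| Assumed k | SE | Power at 5% | Power at 5%/3 |
|---|---|---|---|
| 0.25 | 0.044 | 99% | 98% |
| 0.35 | 0.054 | 96% | 90% |
| 0.40 | 0.060 | 92% | 83% |
| 0.50 | 0.071 | 80% | 66% |

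**The case against.** **The analysis plan is deferred.** Data analysis says the detailed plan will be finalized later, so the lack of a multiplicity method is not in itself a defect of this article. That stands. It does not excuse three conflicting lists, differing definitions and a tested outcome missing from the primary list, all of which are printed here.

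**A confirmatory core can be read from the text.** Sample and sample size and Hypothesis testing name the same three outcomes, and mortality is expressly not primary. This is fair, and it is why the fix builds on those three. But the section actually headed Primary outcomes does not match that core.

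**H1 may require all five practices to improve.** On that reading, 5% per test does not inflate the error. The text neither adopts nor excludes it, so the inflation figures are conditional on any single success being enough.

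**Stronger readings that the document does not support:**

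- A reader might infer that a chance primary success is more likely than not. Twelve independent tests give 46%, with harm counted as well as benefit. Counting the double cut-offs as fourteen independent tests gives 51%, but four visits imply two and a 24-hour delay implies a 6-hour one, so those tests are not independent. Twelve is itself generous, because sepsis management is not a single proportion; eleven tests give 43%.
- A reader might infer that a difference of about 9 ANC points would be taken as confirming H1. That figure (1.96 × 0.044 = 0.086) rests on the assumed 17 women per village and village-level k of 0.25. The planned relative risk with its 95% interval would also let readers see how far a result fell short of the target.
- A reader might infer that community health worker knowledge, part of the sepsis item, has no control counterpart. The study trained workers for intervention villages, but no section says that comparison villages have none; the article describes village health teams as existing nationally, though mostly not functional.

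**Conclusion.** The point holds as an inconsistency that should be corrected before evaluation. The protocol contradicts itself on which outcomes are confirmatory, on the postnatal care target, and on how breastfeeding initiation and delivery care are defined. It applies 5% throughout with no rule for success.

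If any one of the twelve primary items would do, the family-wise false-positive rate is at most about 46% in either direction and about 26% for a false benefit. At correlations from 0.7 down to 0.3 it is about 23–40% and 12–20%. Even the lowest of these is more than four times the rate for a single test. The range assumes two-sided tests, one test per bullet and a common correlation. It does not apply if success requires every outcome to improve.

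**What to change.** - Make ANC at least four times, skilled attendance and postnatal care the only primary outcomes, with Holm control at 5% overall.
- Make all other items secondary, reported with confidence intervals.
- Use one definition per outcome in Primary outcomes and Table 4: one breastfeeding window, one delivery-care term, and one ANC cut-off for the primary outcome.
- Reconcile the postnatal care target between Sample and sample size (24%) and H1 and Hypothesis testing (50%).
- State H1 as superiority, with the target effects as planning values against which the confidence interval is judged.
- Because the trial is registered and under way, record this as a dated amendment, with its reason, made before the evaluation data are analysed. It shortens the primary list and adds postnatal care to it, so it is a change of outcomes and not only of wording.

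The cost is some power. On the parish basis, power for the three outcomes at the strictest Holm step falls from about 80% to 66–68%. On the assumed village basis, ANC power at that step is about 98% at k = 0.25, 83% at 0.40 and 66% at 0.50. The analysis plan should state the village-level k and the interviews per village, so that the loss can be judged.

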## Background

Maternal and neonatal illness represent some of the most important health conditions in Uganda and in sub-Saharan Africa (SSA). Globally, of the 7.6 million deaths of children under five years each year [1], 3.6 million (41%) are deaths of babies in the neonatal period, and 98% of these deaths occur in developing countries. Although recent reports show some improvements in maternal mortality globally from the current estimate of 342,900 maternal deaths worldwide in 2008, down from 526,300 in 1980 [2], there has been minimal change in sub-Saharan Africa [2].

Most neonatal deaths, or death within the first month of life, take place on the day of delivery; between 30 and 50% of newborn deaths in Africa are on the first day of life, and 75% occur in the first week alone. The same is true for maternal deaths - approximately 50% of maternal deaths take place within one day of childbirth. A number of factors contribute to this high maternal and newborn mortality including the low (37%) skilled attendance at births, poverty, HIV/AIDS, low-quality antenatal and delivery care, and the unavailability of postnatal care on the continent, as most births occur at home due to problems related to inaccessibility to care.

Despite high use of antenatal care (ANC) (94% for the first ANC visit) in Uganda [3], deliveries at health facilities have remained low (42%), and Emergency Obstetric Care (EmOC) met need is only 14%. Postnatal care (PNC) coverage is very low and maternal mortality, perinatal and neonatal mortality have remained high (maternal mortality ratio 435 per 100,000 live births, perinatal mortality 36 per 1,000 and neonatal mortality 29 per 1,000 live births) [3].

To date, most efforts to improve maternal and newborn health in Uganda have focused on influencing the supply side, usually involving training of health workers, provision of supplies, and health education. Few interventions have been directed at influencing the community or the demand side. Previous efforts in safe motherhood and child health generally neglected newborn care, with the consequence that efforts to achieve Millennium Development Goal (MDG) 4 are currently greatly constrained by a relatively high proportion of neonatal deaths. In addition, focus has been on facility-based care with limited linkages between the facilities and the community.

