**Figure 1 F1:**
[figure not shown]
Map showing the location of Iganga-Mayuge districts and the Demographic Surveillance Area, Uganda.

The Iganga-Mayuge DSS started its operations in 2004 as collaboration between Makerere University and the Karolinska Institutet, Sweden on one hand, and the two host districts on the other, with seed funding from Sida/SAREC. The Demographic Surveillance Area (DSA) has a population of about 67,200 people in 63 villages, 18 parishes and 12,000 households.

Through household visits, field assistants record pregnancies, pregnancy outcomes, deaths and migrations. Since November 2005, village-based demographic scouts notify DSS verbal autopsy interviewers (VAI) of all deaths in the area as they occur on a continuous basis. The VAI visit the bereaved family a month after the event and interview a relative of the deceased who was present at the time of the illness/event and death on verbal and social autopsies (VASA). Three experienced practising doctors independently review the data and assign differential diagnoses on the cause of death according to standard criteria. If there is agreement between at least two of them, the diagnosis is accepted as the definitive cause of death. However, if they do not agree, the three doctors meet to discuss the case and attempt to reach agreement. If this is not possible the cause is coded as undetermined. Besides determination of the most prevalent causes and circumstances of death, we also use the data to profile the burden of different disease, including neonatal conditions. This data from the VASA for maternal and newborn deaths will be analysed as part of the formative research. Results will be used to identify areas in the social processes leading up to death and hence identify modifiable factors in the home or health system on which interventions can be designed.

Iganga Hospital and 13 small health units of which 2 conduct deliveries are located in the DSA. Preliminary findings from the DSA show the following: that 60% of all deaths occur outside a health facility setting; almost all (90%) deaths are due to illnesses as opposed to other causes like injuries and suicide; and the stillbirth rate is about 10/1,000 births, thus indicating under-detection of negative birth outcomes. As it is for most DSS, the first analysis has been a learning experience on the quality of the data, particularly on the reporting of pregnancies, births and newborn deaths.

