**Health facility strengthening**		
• Training	• Sepsis	• Poor quality of care, low HF use for deliveries, inadequate equipment
• Provision of supplies and medicines	• Sepsis	
• Improved sepsis management at lower HF	• Sepsis	
• Supervision and monitoring	• Overall risk	

EPI, expanded programme of immunization; IPT, intermittent presumptive treatment; ITN, insecticide-treated net; HF, health facility; PMTCT, preventing mother-to-child transmission; TT, tetanus toxoid immunization.

The way that these interventions are likely to affect neonatal mortality from infection is by reducing the risk of infection, improving the management of infection, improving the timing of management of infection, improving compliance with treatment. These improvements would likely reduce the proportion of neonatal deaths from infection significantly. We will monitor the different components to be sure that there is solid understanding of how mothers respond to the community visits, and how facilities respond to referred infants. With regard to other causes of neonatal death, birth asphyxia may be improved by increasing attendance at deliveries by skilled attendants, and by identification of risk pregnancies - with appropriate referral. Neonatal deaths from prematurity and low birth weight can be prevented by early identification of risk infants, and appropriate care at home and at a facility.

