While not a primary outcome, variable stillbirth rate and neonatal mortality rate will be followed through the study in both intervention and control areas. We will define miscarriage as cessation of a presumptive pregnancy before 28 weeks of gestation and stillbirth as fetal death after 28 weeks of gestation but before delivery of the baby’s head, which was a modification of the 22-week definition to meet local practicalities. We will classify neonatal death as death of a live born infant within 28 completed days of birth. Early neonatal deaths will refer to deaths within 7 completed days after delivery. Separate analysis will be done for neonatal mortality excluding the first day of life in order to assess the role of sepsis.

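### Neonatal mortality after day one is an all-cause timing measure and does not isolate sepsis; the assigned causes of death should carry that question

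*Protocol article*

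**What the plan says.** The last paragraph of Additional analyses (protocol article) sets out how stillbirth and neonatal mortality will be followed. Neonatal death is defined as "death of a live born infant within 28 completed days of birth", and "Early neonatal deaths will refer to deaths within 7 completed days after delivery". The paragraph ends: "Separate analysis will be done for neonatal mortality excluding the first day of life in order to assess the role of sepsis".

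Four other parts of the article bear on this:

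- **Study site.** Deaths in the surveillance area are followed by an interview with a relative. "Three experienced practising doctors independently review the data and assign differential diagnoses on the cause of death according to standard criteria". Agreement of at least two doctors fixes the cause. Otherwise the three meet to seek agreement, and "If this is not possible the cause is coded as undetermined".
- **Table 4, impact level.** For newborn deaths and stillbirths, "we will explore each maternal and newborn death using the VASA" and a case-control study.
- **Background.** On timing, "between 30 and 50% of newborn deaths in Africa are on the first day of life, and 75% occur in the first week alone".
- **Pathways to effect in intervention.** The package is expected to act on infection, but not on infection alone: "Neonatal deaths from prematurity and low birth weight can be prevented by early identification of risk infants" and appropriate care, and birth asphyxia may improve through skilled attendance at delivery.

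Study outcomes makes neonatal mortality a secondary outcome and states that the study is not powered for it.

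**The concern.** The sentence ties a method to an inference. The method selects deaths by age. The inference is about one cause. Nothing in it restricts the deaths to those judged to be infective, and it makes no link to the causes that the site's doctors assign.

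If mortality after day one differed between arms, sepsis would be one explanation among several that the article itself puts forward. Care of low-birth-weight babies could produce the same pattern and be reported as an effect on sepsis. Conversely, a real effect on sepsis could be diluted by deaths from other causes, and any sepsis death on day one is left out by construction.

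This matters because infection is central to the article's account of how the package works, effectiveness of sepsis management is listed among the primary outcomes, and the Discussions section says the study is designed to influence policy directly.

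**Working it through.** The article gives no figure for this analysis, so there is none to reproduce. The check has three steps.

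**1. How much of the retained mortality is still early?**

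Inputs from the Background: share of neonatal deaths on day one, d = 0.30 to 0.50; share in the first week, 0.75, read as including day one. These are figures for Africa, assumed here to apply to the site.

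- Share of retained deaths in the rest of week one = (0.75 − d) / (1 − d)
- Share in weeks two to four = 0.25 / (1 − d)

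| d | Rest of week one | Weeks two to four |
|---|---|---|
| 0.30 | 0.45 / 0.70 = 64.3% | 0.25 / 0.70 = 35.7% |
| 0.40 | 0.35 / 0.60 = 58.3% | 0.25 / 0.60 = 41.7% |
| 0.50 | 0.25 / 0.50 = 50.0% | 0.25 / 0.50 = 50.0% |

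Half to nearly two-thirds of the deaths kept are therefore still early neonatal deaths.

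**2. How much of the retained mortality is sepsis?**

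The article does not say. Let e be the sepsis fraction in the rest of week one and l the fraction in weeks two to four. Both are assumptions, varied widely: e from 0.10 to 0.60 and l from 0.50 to 0.90.

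- Sepsis share = [(0.75 − d) × e + 0.25 × l] / (1 − d)
- Lowest (d = 0.30, e = 0.10, l = 0.50): (0.045 + 0.125) / 0.70 = 24%
- Highest (d = 0.50, e = 0.60, l = 0.90): (0.150 + 0.225) / 0.50 = 75%

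The range illustrates what is unknown and is not an estimate. It shows that the sepsis content of the measure cannot be fixed from the article.

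**3. Could other causes move the measure?**

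Yes, on the article's own account. Table 1 places postnatal visits from the day of birth to day 2, on day 3 and on days 5 to 7, with support for warmth and feeding. Home visits by CHWs adds at least two visits to low-birth-weight babies in their second week. The package therefore works on non-infective risk inside the retained window, in its later part as well as its early part. Pathways to effect in intervention expects that work to prevent deaths.

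Together, a difference between arms after day one is what the article would predict from sepsis, from prematurity and low birth weight, or from both. The age filter cannot tell these apart.

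**The case against.** The strongest reply is that this is one separate, exploratory analysis of an outcome that the article openly calls unpowered, and that cause of death is not ignored. Table 4 plans to examine each newborn death with the verbal and social autopsy and a case-control study, special studies of sepsis management are listed, and the detailed analysis plan was still to be finalized. Age at death also does not depend on verbal-autopsy coding, which rests on a relative's interview a month after the death and leaves some causes undetermined. All of this stands. It keeps the point small and is a good reason to retain the timing analysis. It does not rescue the stated purpose, because Additional analyses assigns the sepsis question to the timing measure.

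Stronger readings are tempting, but the documents do not support them:

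- **That the measure will consist largely of other early deaths.** An early death is not necessarily a non-sepsis death, and no cause split by age is given. Non-sepsis early deaths would exceed half of the retained deaths only if sepsis caused less than 1 − 0.35/0.45 = 22% of rest-of-week-one deaths at d = 0.30, or less than 1 − 0.30/0.35 = 14% at d = 0.40. At d = 0.50 they cannot exceed half.
- **That a cause is available for every death.** Some will be coded undetermined.
- **That starting after day one biases the comparison by conditioning on survival.** No denominator is fixed, and deaths per live birth would not condition on it. The cause-specific measure shares the underlying issue, since a baby saved on day one may later die of sepsis.
- **That a number of affected deaths can be stated.** This would need site rates. The Background and study context give national ones, and Study site reports under-detection of negative birth outcomes.

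**Conclusion.** The point holds in a limited form. Mortality after day one does not isolate sepsis and cannot by itself support a conclusion about sepsis. On the article's timing figures, 50 to 64% of the retained deaths fall in the first week. This assumes that the African figures apply to the site and that the 75% includes day one. The cause mix of those deaths is not given, so the size of any misattribution, and its direction, cannot be stated.

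The issue is minor. It concerns a secondary, unpowered outcome and leaves every primary outcome, hypothesis and sample size untouched. It is still more than a missing detail, because it changes what the trial may say about sepsis.

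**What to change.** Replace the sentence in Additional analyses with wording to this effect:

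- The role of sepsis will be assessed descriptively by neonatal deaths with infection or sepsis as the physician-assigned cause from the verbal and social autopsy, per 1,000 live births by arm.
- Deaths coded undetermined will be reported by arm.
- The doctors will assign causes without the trial arm or CHW-visit information, where feasible.
- Neonatal mortality excluding the first day will also be reported, labelled as all-cause mortality after day one, with no conclusion about sepsis drawn from it alone.

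The cost is one short change of wording plus removal of the arm and visit fields from the coding material. The site already produces the cause codes, so no new data are needed. The downsides are fewer events than in the all-cause count and some misclassification by verbal autopsy, so the result remains descriptive.
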